### Statistical methods

The primary study endpoint will be the absolute risk reduction (ARR) with 95% confidence intervals (CIs) based on the proportion of volunteers in each arm with absence of PCR-positive parasitemia at the end of 6 months using an intention-to-treat analysis (Table 1). In addition, logistic regression modeling may be employed to provide multivariate analyses based on other possible study confounders such as age, proportion of children, proportion of pregnant women, etc. The primary study population will be intention-to-treat, defined as all volunteers (both military and civilian family members) who are enrolled at either site. The per-protocol analysis population will include all those volunteers who enrolled and completed follow-up up to 180 days. However, volunteers lost to follow-up that do not complete up to 180 days of follow-up will be excluded from the per-protocol analysis, but included in an intention-to-treat analysis.

Secondary study endpoints are pilot endpoints to include incidence rates, molecular and parasitological endpoints, safety, vector control effectiveness (e.g., permethrin-treated versus water-treated uniforms), and comparison of malaria and G6PD diagnostic modalities. The calculation of incidence rates (attack rate over total time at risk) for prophylactic and FSAT groups will be calculated adjusted and unadjusted with 95% CI. All volunteers completing at least one follow-up assessment will be included in the safety analysis. The safety analysis database will include those volunteers in the set of randomized volunteers who receive at least one dose of study drug. All parasitological data will be included in the parasitological analyses. A stratified analysis comparing the vector control arms within each group will also be compared as those remaining malaria-free at 180 days. Given the possibility of the highly variable nature of transmission at the geographical sites, existing pre-enrollment malaria surveillance data by RCAF and day 1 screening data by AFRIMS will guide if a pair-matched analysis is necessary.

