### Aim and objectives

We present a pilot operational research protocol to investigate the effectiveness of monthly prophylactic drug administration compared to a focused screen-and-treat approach to inform a regional malaria elimination initiative by the Royal Cambodian Armed Forces (RCAF).*Primary objective*: to compare the effectiveness of focused screening and treatment (FSAT) following current national treatment guidelines versus monthly malaria prophylaxis (MMP) with dihydroartemisinin-piperaquine (DHA-PIP) in combination with weekly primaquine (PQ) (22.5 mg) as transmission-blocking and radical curative agent to reduce the risk of malaria infection in personnel residing in military encampments on the Thai-Cambodian border*Secondary objectives*:◦ To estimate the incremental benefit of wearing a permethrin insecticide-treated uniform (ITU) over drug therapy and existing vector control interventions compared to a sham insecticide-treated uniform (sITU) treated with water. Civilian participants will have comparable selected outer garments treated◦ To define the proportion of asymptomatic carriers of malaria in the population, including the cumulative incidence and incidence density of microscopic and submicroscopic blood-stage parasitemia and gametocytemia◦ Additional secondary objectives can be found in Table 1/Additional file 1

**Table 1 Tab1:** Outcomes

Objectives	Outcomes/endpoints
Primary	
To compare the effectiveness of focused screening and treatment (FSAT) following current national treatment guidelines versus targeted monthly malaria prophylaxis (MMP) with DHA-piperaquine in combination with low-dose weekly primaquine (PQ) (22.5 mg) for 12 weeks	Absolute risk reduction in a cluster based on those individuals’ polymerase chain reaction (PCR)-corrected absence of parasitemia at the end of 6 months in the MMP versus FSAT clusters
Secondary	
Estimate the incremental benefit of insecticide-treated uniforms (ITU) over drug therapy and existing vector control interventions compared to a sham insecticide-treated uniform (sITU)^a^	Absolute risk reduction in a cluster based on those individuals’ PCR-corrected absence of parasitemia at the end of 6 months^a^ Proportional landings of mosquitoes on treated uniform’s swatch side of cages

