Because observations of individuals in the same geographical area (e.g., cluster) are correlated (non-independent), the effective sample size needed is larger than an individualized randomized trial. Given that the intracorrelation coefficient (ICC) is not known, we assumed a conservative value of 0.4. To detect a minimum of a two-fold difference in the effectiveness of MDA over FSAT in proportion of volunteers being malaria-free at 6 months with an α = 0.05 and 80% power, the number needed in each cluster is at least 78 individuals [28]. Given that the number of clusters is limited based on RCAF organization and patrolling areas, our proposed cluster number of 8 with a size of 80–140 volunteers per cluster would be sufficient even at higher (e.g., more conservative) values of ICC (> 0.4).

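### The primary risk reduction and its 95% CI are described at volunteer level with no allowance for clustering named, although eight encampments are randomised and an ICC of 0.4 is assumed

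*Protocol article*

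**What the plan says.** **Analysis.** Under Statistical methods, the primary endpoint is the "absolute risk reduction (ARR) with 95% confidence intervals (CIs) based on the proportion of volunteers in each arm with absence of PCR-positive parasitemia" at six months, by intention to treat. The section adds that "logistic regression modeling may be employed to provide multivariate analyses", and that incidence rates will be given with 95% CIs, adjusted and unadjusted. It names no variance method for any of these. Because transmission may differ between sites, pre-enrolment surveillance and day 1 screening data "will guide if a pair-matched analysis is necessary".

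**Design.** Under Cluster randomization, allocation, and blinding, geographical areas are allocated 1:1. The Abstract and the Sample size rationale give eight clusters, so four per arm. The Sample size rationale recognises the consequence: "Because observations of individuals in the same geographical area (e.g., cluster) are correlated (non-independent), the effective sample size needed is larger". It says the ICC is unknown and that "we assumed a conservative value of 0.4".

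**Endpoint table.** Table 1, under Aim and objectives, begins the same primary endpoint with "Absolute risk reduction in a cluster based on those" and goes on to the individuals' PCR-corrected status at six months.

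**The concern.** The unit of randomisation is the encampment, but the only unit named for the primary estimate and its interval is the volunteer, aggregated by arm. The correlation that enlarges the sample size is not carried into the analysis. Two places in the article therefore give different units for the primary endpoint, and the one in Statistical methods, followed as it stands, leads to an ordinary two-proportion interval.

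With four clusters per arm, the information about MMP versus FSAT lies mainly between encampments. An interval built on about 1000 independent people would attribute ordinary differences between encampments to the strategy. The Limitations section concedes that few clusters may reduce power. It says nothing of the opposite risk, an interval that is too narrow. The article itself expects transmission to vary a good deal between sites, so a negligible ICC would be hard to defend.

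**Working it through.** **Inputs**
- Clusters: 8, allocated 1:1, so 4 per arm.
- Cluster size m: 80 to 140 (Sample size rationale). About 1000 people / 8 = 125 (Abstract). The maximum of 1200 / 8 = 150.
- ICC: 0.4 assumed in the article. I add 0.01, 0.05 and 0.1 as a range because the true value is unknown.
- Malaria-free proportion: 50% under FSAT. For MMP, 100% as planned, and 90% as an alternative.

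**The plan's own figure.** The Sample size rationale gives at least 78 per cluster. I could not reproduce it with 4 clusters per arm and ICC 0.4. At 50% v 100%, two-sided, the unpooled formula gives about 6 per cluster. The pooled formula needs 10.5 effective volunteers per arm, while ICC 0.4 caps four clusters at 4/0.4 = 10. That is a separate matter, and nothing below depends on the 78.

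**Step 1: design effect and standard error.** DE = 1 + (m − 1) × ICC, and the unadjusted SE is too small by √DE. At m = 125 and ICC 0.4, DE = 1 + 124 × 0.4 = 50.6 and √DE = 7.1. At ICC 0.4, √DE is 5.7 for m = 80 and 7.8 for m = 150.

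**Step 2: chance that an unadjusted 95% interval excludes zero when the arms do not differ.** This is approximately 2 × [1 − Φ(1.96/√DE)].

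| ICC | DE, m = 80 | Error, m = 80 | DE, m = 125 | √DE, m = 125 | Error, m = 125 |
|---|---|---|---|---|---|
| 0.01 | 1.79 | 0.14 | 2.24 | 1.50 | 0.19 |
| 0.05 | 4.95 | 0.38 | 7.20 | 2.68 | 0.47 |
| 0.1 | 8.90 | 0.51 | 13.4 | 3.66 | 0.59 |
| 0.4 | 32.6 | 0.73 | 50.6 | 7.11 | 0.78 |

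A beta-binomial simulation (40,000 runs, 4 v 4 clusters) agrees. With m = 125 and both arms at 50%, the unadjusted interval excludes zero in 0.20, 0.47, 0.60 and 0.79 of runs. Across the settings run, an unweighted t-test on the eight cluster proportions rejects in about 0.02 to 0.06.

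**Step 3: interval half-widths at m = 125 (500 per arm).**
- Both arms at 50%: unadjusted 1.96 × √(2 × 0.25/500) = 6.2 points. Adjusted with t on 6 df: 2.447 × √(2 × 0.25 × DE/500) = 55 points at ICC 0.4, 21 at ICC 0.05 and 12 at ICC 0.01.
- 50% v 100%, ICC 0.4: unadjusted 1.96 × √(0.25/500) = 4.4 points, adjusted 2.447 × √(0.25 × 50.6/500) = 39 points. Using 6 df is generous here, because an arm that is entirely malaria-free contributes no variance.
- 50% v 90%, ICC 0.4: unadjusted 1.96 × √((0.25 + 0.09)/500) = 5.1 points, adjusted 2.447 × √(0.34 × 50.6/500) = 45 points.

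So at ICC 0.4 the planned 50-point difference exceeds its adjusted half-width (39), but a 40-point difference does not exceed its own (45).

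**The case against.** The strongest reply is that this reads a method into a silence. A proportion per arm is a normal point estimate in a cluster trial, and a cluster-robust interval would fit the same sentence. No CI formula is given. Some text points towards the cluster: Table 1's wording, the Abstract's reference to distinct encampments, the pair-matched option, and logistic covariates that include aggregate quantities such as the proportion of children. This is a condensed article, and a variance method may sit in an analysis plan that is not shown. The trial is called a pilot, reports an estimate with an interval rather than a declared test, and accepts that its clusters are few. The largest error figure needs an unadjusted interval and an ICC that the authors call unknown and conservative.

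Much of this stands. A reader might infer that the investigators will analyse about 1000 volunteers as independent, or that the trial has an 80% false-positive rate. The article supports neither statement: it never says that clustering will be ignored, and the error rate depends on the ICC.

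What remains is a mismatch in stated text, not merely missing detail. Statistical methods fixes volunteer and arm as the level of the primary estimate, while Table 1 and the Sample size rationale point to the cluster. The pair-matched option is conditional and does not say what happens if it is not used. Pilot status and the admission of low power do not cover an interval that is too narrow, particularly as the article expects its results to inform a national strategy.

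**Conclusion.** The point holds as a mismatch that needs correcting. The primary ARR and CI are described at volunteer level with no cluster adjustment named, against a design, a sample size premise and an endpoint table that rest on clusters. The ARR point estimate is not in question; its standard error and interval are.

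If the text is followed literally with equal clusters of 125, the SE is about 7 times too small at ICC 0.4 and about 1.5 times at ICC 0.01. The chance of a spurious exclusion of zero is about 0.78 and 0.19 respectively, against a nominal 0.05. These sizes assume an unadjusted interval, equal cluster sizes and no gain from the region-blocked randomisation. The conclusion does not depend on the value 0.4, because the error is well above nominal at every ICC examined.

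**What to change.** - Reconcile Statistical methods with Table 1. State that the primary CI and test use the malaria-free proportion of each cluster, with the ARR as the difference between arm means of these proportions, or use a cluster-adjusted model with a small-sample correction. Use t on 6 df if unmatched (8 clusters − 2 arms) and 3 df for four matched pairs (4 − 1).
- State how clusters are weighted, since sizes of 80 to 140 can make the mean of cluster proportions differ from the volunteer-weighted proportion.
- Decide on pair-matching from the surveillance and day 1 data before any outcome data are seen, and record the decision.
- Fit the logistic and incidence-rate analyses with cluster-adjusted methods.
- Do not carry 6 df over to the uniform comparison. It is made within each arm, so only four clusters contribute (two v two if balanced, which I assume). Use degrees of freedom that reflect this, or report it descriptively.

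The cost is a few sentences and minor programming. The intervals will be wider, and at ICC 0.4 much wider.

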### Treatment intervention

Volunteers randomized to MMP arm aged 13 years and older receive a monthly 3-day treatment course of (DHA-PIP; 360/2880 mg) for 3 months. They will also receive a weekly dose of 22.5 mg of PQ for 12 weeks. Children of 12 years of age or less will receive only a monthly 3-day weight-based treatment dose of DP for 3 months without PQ treatment. In the MMP arm, symptomatic patients or microscopy-confirmed parasitemia in the first 3 months are considered a failure of prophylaxis and treatment is given according to the national treatment guidelines. If the volunteer has parasitemia detectable by PCR only and is symptom free at monthly follow-up, the study treatment with monthly DHA-PIP is continued for 3 months as outlined for the MMP arm. To reduce phlebotomy requirements for G6PD testing and potential hemolytic risk in children, PQ is not be administered to those less than 13 years old.

Volunteers randomized to the focused screening and treatment (FSAT) arm are treated according to current national malaria treatment guidelines if they test positive for malaria based on blood smear and/or real-time PCR results during monthly follow-up. In the FSAT arm, all volunteers with parasitemia detectable with PCR receive antimalarial treatment, even if they are symptom- free.

At the time of protocol development, national treatment guidelines for areas of known piperaquine resistance, to include the designated study regions, recommended a 3-day course of artesunate and mefloquine (A + M) and a single 15-mg dose of PQ for acute *P. falciparum*, or DP for blood-stage *P. vivax* infection. Elimination interventions are carried out monthly during the first 3 months after enrollment, and then followed by 3 months of additional malaria assessment by smear and PCR diagnosis with malaria treatment as necessary following current national treatment guidelines (Fig. 1, Table 2, Fig. 2). Those febrile but negative for malaria are referred for evaluation and treatment of alternative diagnoses.

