### Sample size rationale

Up to 1200 persons are being enrolled and followed in this cluster-randomized study. The study compares estimates of the absolute risk reduction based on the proportion remaining malaria free at the end of 6 months. We assume that MMP administration combined with an insecticide-treated uniform (ITU) on the background of any pre-existing vector control methods that might be employed will need to reduce malaria incidence to zero by study conclusion to achieve elimination. The MMP approach will be using nearly every currently available intervention in Cambodia to eliminate malaria in this population. Current mathematical models show that multi-round mass drug administration (MDA) can reduce malaria prevalence to less than 10% if high coverage is achieved [27]. Focused screening and treatment alone (FSAT) is assumed to be 50% effective based on a recent study at the same site which found that only 50% of patients treated using an intense screening and treatment approach remained malaria free at the end of 4–6 months of follow-up [2]. The study is, therefore, powered to detect a two-fold difference in effectiveness between the two intervention groups. These are thought to be reasonable assumptions a priori for the purposes of sample size calculations though there has never been a head-to-head comparison of these strategies published in the literature. Given that this will be a stratified analysis, no assumptions regarding vector control measures are included in the calculation. Pre-existing vector control measures that the Military may employ, including ITNs, are assumed to be equally distributed among the overall study population. Permethrin-treated uniform comparisons are a secondary endpoint intended only to estimate a potential additive effect.

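### The primary endpoint is a single-day parasitaemia status in the analysis but a cumulative malaria-free proportion in the sample size, so the 50% planning risk and 80% power do not belong to the endpoint as written

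*Protocol article*

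**What the plan says.** The protocol article describes the primary outcome in several places.

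- **Statistical methods:** the absolute risk reduction (ARR) rests on the proportion of "volunteers in each arm with absence of PCR-positive parasitemia at the end of" 6 months, by intention to treat.
- **Table 1 (primary outcome):** it rests on "polymerase chain reaction (PCR)-corrected absence of parasitemia at the end of" 6 months, compared between MMP and FSAT clusters.
- **Limitations:** the outcome is the ARR at 24 weeks.
- **Sample size rationale:** the study compares estimates of the "absolute risk reduction based on the proportion remaining malaria free at the end of" 6 months. FSAT is taken as 50% effective because, in a recent study at the same site, only half "of patients treated using an intense screening and treatment approach remained malaria free" at the end of 4–6 months. MMP is assumed to bring incidence to zero.

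The Treatment intervention section shows what happens to infections found on the way. Every PCR-positive FSAT volunteer is treated. A symptomatic or smear-positive MMP volunteer in the first 3 months is "considered a failure of prophylaxis and treatment is given according to the national treatment guidelines". A symptom-free MMP volunteer positive by PCR only continues study drug in that period. In months 4–6, infections in both arms are treated as needed, and Limitations says the MMP arm then reverts to standard of care. No section says how an infection treated before day 180 counts in the primary endpoint.

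**The concern.** If infections were left untreated, being parasite-free at month 6 and having stayed malaria free to month 6 would be nearly the same. Here most detected infections are treated at monthly visits, so the two separate. A volunteer who fails prophylaxis in month 2, is treated and tests negative on day 180 is a failure under the sample size wording and a success under the analysis wording. The day-180 status also follows three months in which both arms receive similar care, so it mainly reflects recent or uncleared infections.

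Two things are at stake. Two analysts could score the same volunteer in opposite ways, each with support in the text. And the power statement uses a cumulative risk that cannot be carried over to a point prevalence.

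**Working it through.** **Inputs from the article.** FSAT 50% malaria free; MMP 100% (zero incidence); α = 0.05, taken as two-sided; 80% power; ICC 0.4; 8 clusters at 1:1, so 4 per arm; at least 78 per cluster, planned size 80–140.

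**Step 1: the plan's own figure.** Effective size per arm = 4m / [1 + (m − 1) × ICC]. With m = 78: 312 / (1 + 77 × 0.4) = 312 / 31.8 = 9.81.

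Power = Φ[(d − 1.96·se0) / se1], where se0 = √[2p̄(1 − p̄)/n] and se1 = √{[p1(1 − p1) + p2(1 − p2)]/n}.

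For risks of 50% vs 0%: se0 = 0.1955, se1 = 0.1596, and (0.5 − 0.3832)/0.1596 = 0.732, so power is 76.8%. This is close to the stated 80% but does not reproduce it. That shortfall is a separate matter. What counts here is that the stated power is roughly consistent with 50% vs 0%, a cumulative contrast.

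**Step 2: what 50% cumulative means on one day.** The article gives no figure for this, so it needs assumptions: a constant monthly risk h, and a proportion c of infections cleared at each monthly visit.

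- 50% over 6 visits: h = 1 − 0.5^(1/6) = 0.109.
- 50% over 4 visits: h = 1 − 0.5^(1/4) = 0.159.

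Prevalence found at a visit is q = p + (1 − p)h, where p is the prevalence left after the previous visit. After treatment, p = q(1 − c), starting from p = 0.

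| Cure at each visit | 6 visits | 4 visits |
|---|---|---|
| 100% | 10.9% | 15.9% |
| 80% | 13.3% | 19.1% |
| 50% | 19.5% | 26.6% |
| 0% | 50% | 50% |

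Only with no cure does the single-day figure return to 50%.

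**Step 3: power at these risks.** MMP 0%, ICC 0.4, 4 clusters per arm, 78 per cluster. The t column uses a noncentral t with 6 df and noncentrality d/se1.

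| FSAT risk | se0 | se1 | Normal | t |
|---|---|---|---|---|
| 10.9% | 0.1025 | 0.0995 | 18% | 15% |
| 20% | 0.1354 | 0.1277 | 30% | 26% |
| 26.6% | 0.1533 | 0.1411 | 40% | 35% |
| 50% | 0.1955 | 0.1596 | 77% | 74% |

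With 125 per cluster the t value at 50% is about 75%. A beta-binomial simulation at that size gives about 73% at 50% and about 5% at 10.9%. Without clustering, the number needed per arm rises from 11 (50% vs 0%) to 67 (10.9% vs 0%).

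**Step 4: sensitivity to the ICC.** At ICC 0.1 and 78 per cluster, the normal approximation gives 53% at 10.9% and 82% at 20%. The loss is therefore largest at the plan's own ICC and smaller if clustering is weak.

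**The case against.** The strongest reply is that the single-day reading is literal wording and not a stated rule, and that other text leans towards the cumulative one. The Abstract speaks of risk reduction for malaria infection, and the primary objective is to reduce that risk. Early MMP infections are labelled prophylaxis failures. Statistical methods itself uses remaining malaria-free at 180 days for the uniform comparison, which shares the primary's Table 1 wording. On the cumulative reading the 50% fits and power is about 75–77%. This stands as far as it goes: the plan does not positively declare cured infections to be successes. But nothing says they are failures, and the sentence that defines the primary analysis gives the single-day status.

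A second reply is that residual infection at month 6 is a sensible endpoint for elimination, that Limitations openly describes intervening, reverting to standard care and monitoring, and that cumulative incidence and incidence density are listed as secondary outcomes. That also stands. The earlier infections are not lost to the trial, and a day-180 endpoint is defensible. It would still need its own planning risk.

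Three stronger readings are tempting, and the documents do not support them.

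- **New infections discounted.** A reader might infer this from the term PCR-corrected in Table 1. The Microscopy section uses PCR correction for confirming smears, and Table 1 also attaches the term to absence of gametocytaemia. Only the recrudescence outcome plainly needs genotyping. The term is ambiguous, no more.
- **Lost volunteers counted as malaria free.** A reader might infer this because they stay in the intention-to-treat set. The article says who is in the set and not how missing outcomes are coded, which is commonly left to the SAP.
- **An ARR of at most about 11 points.** That figure is the lower end of an assumption-based range and assumes complete clearance at every visit. The article itself reports reduced DHA-piperaquine efficacy in acute falciparum malaria, and symptom-free PCR-only MMP positives simply continue study drug in months 1–3.

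**Conclusion.** The point holds as an inconsistency in the definition of the primary endpoint, with a direct consequence for the power statement. The analysis wording is a status at one time; the sample size wording and its 50% are cumulative. Since most detected infections are treated, the two are not interchangeable.

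The size is illustrative. With constant monthly risk and 50–100% cure per visit, the 50% becomes about 11–27% on day 180. At ICC 0.4, power against 0% falls from about 75–77% to about 15–18% at 11% and 26–30% at 20%, and lower by simulation at 11%. The study behind the 50% is not shown, and its figure is for treated patients whereas the trial enrols all volunteers, so even the cumulative power takes that figure at face value. The mismatch itself does not depend on any of these assumptions. It should be settled before analysis, because it determines who counts as a failure.

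**What to change.** Use one definition in the Abstract, Table 1, Sample size rationale, Statistical methods and Limitations.

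- **Preferred primary outcome:** any PCR-positive parasitaemia after day 1 through day 180, as a cumulative proportion per cluster, with day-180 PCR prevalence as a key secondary endpoint.
- **Scoring rule:** state that infections treated before day 180 count as failures.
- **Terminology:** state that PCR-corrected means PCR-confirmed in this outcome and does not discount new infections.
- **Sensitivity analysis:** address infections persisting from day 1, for example by restricting to volunteers PCR-negative on day 1. Dropping only the day-30 result would miss later persistence.
- **Alternative:** if the day-180 status is the intended endpoint, keep it, say that earlier treated infections are not failures, and restate the planning risk and power for a prevalence.

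No new data are needed, since Table 2 already schedules monthly PCR. The costs are that early and persistent baseline infections count under the cumulative definition, and that the trial is under way. If the single-day status was the true intent, the preferred option changes the primary outcome and is more than a wording edit. Either way, the choice must be made and documented before outcome data by arm are examined.

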### Study site and population

The study takes place at multiple military encampments in malaria-endemic areas in border areas authorized by the Ministry of National Defense. Sites were chosen based on current malaria incidence estimates by the RCAF health services in consultation with the National Center for Parasitology, Entomology, and Malaria Control (CNM) in Cambodia and the Armed Forces Research Institute of Medical Sciences (AFRIMS). For reasons of operational security, locations or other descriptors will not be further described here. All sites will be evaluated as simultaneously as feasibly possible.

Military volunteers aged 18–65 years of age and their dependents of ≥ 2 years of age, eligible for care at an RCAF facility, or otherwise eligible Cambodian civilians at risk for contracting malaria who live within close proximity, are enrolled if they meet the following criteria: are able to give informed consent/assent; reside in the selected study areas; are available for monthly follow-up for 6 months; agree not to seek outside medical care for febrile illness unless referred by study team; and are authorized by respective military unit commanders to participate in the study if on active duty. Volunteers who have known allergy or other contraindication to study medication; are pregnant, lactating or are women of childbearing age who do not agree to use an acceptable form of contraception during the study; or are judged by the investigator to be otherwise unsuitable for study participation are excluded from the study.

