### Cluster randomization, allocation, and blinding

Geographical areas were randomized prior to study start to a 1:1 allocation of MMP or FSAT using time- and region-blocked randomization to ensure that randomization is geographically distinct, and that malaria incidence is evenly distributed among groups given that high and low transmission areas exist. Volunteers meeting the enrollment criteria receive permethrin- or sham-treated (water-treated) uniforms according to their cluster’s assignment in single-blind fashion (volunteer blinded to assignment but not investigator). Entomology staff conducting uniform testing are also blinded to treatment. Diagnostic microscopists are blinded to each others’ readings and to study arm assignment. There is otherwise no blinding during the study.

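### Whether the eight clusters are analysed in pairs is left to data seen after allocation, with no criterion and no link to the randomisation blocks; one example covariate also conflicts with an exclusion criterion

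*Protocol article*

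**What the plan says.** All references are to the Protocol article.

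- **Allocation**, as described: "Geographical areas were randomized prior to study start to a 1:1 allocation of MMP or FSAT using time- and region-blocked randomization" (section Cluster randomization, allocation, and blinding). The stated aim includes that "malaria incidence is evenly distributed among groups given that high and low transmission areas exist". Neither block size nor any pairing of clusters is described.
- **Number of clusters** (Sample size rationale): "our proposed cluster number of 8 with a size of 80–140 volunteers per cluster", so four per arm at 1:1.
- **Primary analysis** (Statistical methods): the absolute risk reduction (ARR) with a 95% CI, by intention to treat.
- **Pairing** (Statistical methods): because transmission may vary widely between sites, RCAF surveillance from before enrolment and the first-day test results are both to be consulted: "screening data by AFRIMS will guide if a pair-matched analysis is necessary".
- **Adjustment** (Statistical methods): an optional logistic model for "confounders such as age, proportion of children, proportion of pregnant women, etc".
- **Exclusion** (Study site and population): volunteers are not enrolled if they "are pregnant, lactating or are women of childbearing age who do not agree to use an acceptable form of contraception".
- **Day-1 data** (Clinical procedures; Table 2): malaria PCR is done at enrolment for adults and for children. Pregnancy tests are listed at enrolment, at days 30 and 60, and at malaria diagnosis.

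**The concern.** In a cluster trial the analysis should mirror the way clusters were allocated. Here the allocation is described as blocked. Whether the analysis uses pairs is nevertheless to be settled later, from data that include screening results on volunteers enrolled after allocation in an open-label trial. The article does not say what would make pairing necessary, how pairs would be formed, or how they would relate to the blocks.

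With hundreds of clusters this would hardly matter. With eight it changes the reference distribution for the primary interval enough to turn an inconclusive ARR into a conclusive one, or the reverse.

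Two smaller points belong with it. The stated worry is unequal baseline transmission. Pairing is the only remedy named for it, although day-1 PCR status could be adjusted for directly. And one of the three example covariates describes people who cannot be enrolled.

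**Working it through.** The plan gives no figure for the effect of pairing, so there is none to reproduce. Its minimum of 78 individuals per cluster does not enter this point.

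**1. Degrees of freedom by layout.** There are 8 clusters, 4 per arm. For a cluster-level comparison with b blocks, df = 8 − 1 (arm) − b.
- One block (unpaired): 8 − 1 − 1 = 6, critical t (two-sided 5%) 2.45.
- Two blocks (assumed layout, 2:2 in each): 8 − 1 − 2 = 5, critical t 2.57.
- Four blocks of two (pairs): 8 − 1 − 4 = 3, critical t 3.18.

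Two-sided testing is assumed; the article states only α = 0.05.

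**2. Standard errors under the two choices.** Let s1² and s2² be the between-cluster variances in the two arms and c the within-pair covariance, with four clusters per arm.
- Unpaired, pooled: SE² = [(s1² + s2²)/2] × (1/4 + 1/4) = (s1² + s2²)/4.
- Paired: SE² = (s1² + s2² − 2c)/4.

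The sample-size scenario has every MMP cluster at 100% malaria-free. Then s1² = 0 and c = 0, and both formulas give SE = s2/2. The t statistic is identical under both choices and only the critical value differs. The interval is wider under pairing by 3.18/2.45 = 1.30.

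**3. The same in numbers.** Inputs: FSAT 50%, MMP 100%, ICC 0.4 (Sample size rationale), and m = 125 per cluster (about 1000 people over 8 clusters, from the Abstract).
- SE² = (1 + 124 × 0.4) × 0.25 / 500 = 50.6 × 0.25 / 500 = 0.0253, so SE = 0.159.
- An observed ARR of 0.50 gives t = 0.50/0.159 = 3.14, which lies between 2.45 and 3.18.
- Unpaired: 0.50 ± 2.45 × 0.159 = 0.50 ± 0.39, that is 0.11 to 0.89. Zero is excluded.
- Paired: 0.50 ± 3.18 × 0.159 = 0.50 ± 0.51, that is −0.01 to 1.01. Zero is just included.

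Across the stated cluster sizes the result hardly moves. At m = 80, SE² = 32.6 × 0.25/320 = 0.0255 and t = 3.13. At m = 140, SE² = 56.6 × 0.25/560 = 0.0253 and t = 3.14.

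**4. When both arms vary.** A positive c shrinks the paired SE, so pairing can then narrow the interval. The documents give no value for c, so neither choice is better in general. That is a reason to fix it by design.

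**5. Covariates against eligibility.** Pregnant women are excluded at entry, so the proportion pregnant is zero in every cluster at baseline. Any pregnancy detected at day 30 or day 60 arises after allocation and is not a baseline confounder.

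**The case against.** Several points on the other side are sound.

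- **The choice is not outcome-driven.** Both triggers, surveillance before enrolment and day-1 screening, are baseline data. A reader might infer that the plan lets results steer the analysis; the text does not support that.
- **The pairs may be the design.** Block size is not stated. If blocks were of two, the paired analysis would be the correct one and simply deleting the sentence would do harm. One cannot say that pairs are necessarily formed after randomisation.
- **No exact test is planned.** A reader might infer that four pairs can never reach significance, because the smallest two-sided exact p is 2/2^4 = 0.125, against 2/C(8,4) = 2/70 = 0.029 unpaired. The arithmetic is right, but the plan specifies an ARR with a 95% CI, and a paired t analysis on 3 df can exclude zero.
- **A loss of power from pairing is not shown.** In the plan's scenario the two t statistics are the same and one arm has no variance, so only 3 df of variance information exist either way. Using 2.45 there gives a type I error of about 9%, so the narrower unpaired interval is not a genuine gain. For the same reason no power gain from covariate adjustment can be quoted from that scenario.
- **The covariate list is optional and open.** It would be wrong to say that the plan omits day-1 PCR status; it does not name it, and a full list may sit in the analysis plan. The pregnancy item is one example in an optional model and does not touch the primary ARR.
- **Limited power is acknowledged** in the Limitations section.

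What remains is that the article itself states a rule making pairing depend on data seen after allocation, without a criterion and without reference to the blocks. An analysis plan written to match would inherit that rule.

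**Conclusion.** The point holds in this limited form and should be corrected; it does not invalidate the trial. An undetermined choice between 3 and 6 df (critical t 3.18 or 2.45) can decide whether the primary interval excludes zero. In the plan's own target case, an observed ARR of 0.50 sits between the two thresholds. That illustration rests on 100% v 50%, ICC 0.4, 80–140 per cluster, two-sided 5%, and a t-based cluster-level analysis, which the article does not name. Which direction the choice would push the result in the actual data cannot be determined from the documents. The listing of pregnant women as a confounder is a plain inconsistency with eligibility, of minor consequence.

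**What to change.** 1. Replace the pair-matching sentence with a fixed rule: the cluster-level analysis follows the randomisation. State the block layout that was used. Analyse in pairs only if the blocks were pairs; otherwise analyse unpaired, with block as a stratum where degrees of freedom allow.
2. Handle baseline transmission differences by pre-specified adjustment for day-1 PCR status. One workable form has two stages. First, regress the individual 6-month outcome on day-1 PCR status, age group and military/civilian status, without arm. Then take the observed minus expected malaria-free proportion in each of the eight clusters and compare these residuals between arms by t-test (on within-pair differences if the blocks were pairs).
3. Remove the proportion of pregnant women from the example covariates.

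**Cost.** Wording only. Day-1 PCR and age are collected, military or civilian status is known at enrolment, and the blocks are on record from the allocation. If the adjustment is made with cluster-level covariates instead, it costs at most 1–2 df; for example, one covariate in an unpaired analysis takes 6 df to 5 and the critical t from 2.45 to 2.57. The change should be made before outcome data are examined.
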